#### Secondary Outcome

Secondary outcomes included: (1) Changes in BPI-Facial score from baseline to both the week 4 post-treatment and week 16 follow-up phase. The BPI-Facial is a multidimensional pain scale that captures three interference domains: pain intensity, general interference and facial interference. The total score ranges from 0 to 70, with higher scores indicating a greater impact on quality of life (36). (2) Safety assessment. Adverse events occurring during the study, including acupuncture-related syncope, needle breakage, hematoma, and infection, will be recorded in detail along with the corresponding management strategies. If a serious adverse event occurs, the study intervention will be discontinued immediately. Emergency measures will be taken, and the Ethics Committee of the Third Affiliated Hospital of Zhejiang University of Traditional Chinese Medicine will be notified promptly. All adverse events will be classified and reported in accordance with the CONSORT Harms Reporting Guidelines (37).

### Statistical methods

Statistical analyses will be performed using SPSS version 25.0. Baseline characteristics will be summarized for all randomized participants. The modified ITT population will now serve as the primary analysis group, defined as all randomized participants who received at least one treatment session, regardless of protocol adherence or dropout (in line with CONSORT guidelines). Missing data will be handled via multiple imputation (for continuous outcomes) or worst-case sensitivity analysis (for categorical outcomes). Besides, a per-protocol analysis will be reported as supplementary material to assess robustness. Notably, rescue medication (CBZ) use will be included as a time-varying covariate in primary analyses (e.g., mixed-effects models or ANCOVA) to control for its impact on BAI scores. Additionally, sensitivity analyses will stratify participants by rescue medication status (CBZ users vs. non-users) to evaluate whether treatment effects persist independently of CBZ exposure.

Continuous variables will be expressed as mean (SD) percentile otherwise. For measurement data, normality is first assessed. Normally distributed data will be analyzed using *t-*tests, paired *t-*tests, analysis of variance, or analysis of covariance, while non-normally distributed data will be analyzed using *rank-sum* tests (e.g., *Mann-Whitney U* or *Wilcoxon signed-rank* tests). Categorical variables will be analyzed using *chi-square* or *Fisher's* exact tests.

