### Randomization and blinding

Participants will be screened strictly according to the diagnostic criteria, inclusion and exclusion criteria for TN formulate in this trial. The uniquely eligible participants will be numbered by using IBM SPSS Statistics 25.0 software, the relevant parameters will be entered in the syntax editor, and they will be randomly divided into EA and sham EA groups in a 1:1 ratio. Due to the particularly of the acupuncture treatment, a single-blind method will be applied in this study. Importantly, the patients, outcomes assessor, and statistician will be blinded. To ensure better implementation of the blinding method, each participant will be treated individually to minimize discussion about the acupuncture treatment methods, feelings and the therapeutic effects. We will inform the patients that due to individual difference, each person may experience the stimulation differently. At the end of the 4-week treatment period, participants will be asked to indicate whether they had received real EA or sham EA. The proportions of participants who believed they received real EA will then be compared between the two groups.

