### Interventions

The location of acupoints are determined in accordance with the People's Republic of China National Standard, “*Interpretation of China national standard Nomenclature and Location of Meridian Points (GB/T 12346-2021)”* (32). Additionally, all acupuncturists are licensed and experienced physicians. Patients will be treated three times per week for 4 weeks, for a total of 12 EA or sham EA sessions.

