## Limitations

This study has several unavoidable limitations. First, due to the inherent specificity of the acupuncture procedure, blinding the acupuncture operator will not be feasible in our current research design. To mitigate the influence of subjective factors on study outcomes, a third-party evaluator, who are blinded to subgroup allocations, will be engaged to assess results and conduct statistical analysis, thereby enhancing objectivity and impartiality. Nevertheless, this remains a limitation in the experimental design, warranting optimization in future studies. Additionally, a fixed EA protocol will be employed instead of individualized treatment plans based on practitioner experience, potentially introducing performance bias. However, this standardized approach ensured stringent quality control throughout the trial.

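### The primary analysis set leaves out randomised patients who receive no session, and no planned efficacy analysis includes them; the likely bias is small, but avoiding it is cheap

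*Protocol article*

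**What the plan says.** Statistical methods in the protocol article states: "The modified ITT population will now serve as the primary analysis group". The set is "defined as all randomized participants who received at least one treatment session, regardless of protocol adherence or dropout (in line with CONSORT guidelines"). One other efficacy set is named: "a per-protocol analysis will be reported as supplementary material to assess robustness". The baseline table uses a wider set: "Baseline characteristics will be summarized for all randomized participants".

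On missing values the same section says: "Missing data will be handled via multiple imputation (for continuous outcomes) or worst-case sensitivity analysis (for categorical outcomes"). BAI and VAS, the two primary endpoints, are scheduled at baseline, week 4 and week 16 (Table 1).

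On blinding, Randomization and blinding states that "the patients, outcomes assessor, and statistician will be blinded". The Limitations section adds that "blinding the acupuncture operator will not be feasible in our current research design". The acupuncturists deliver both the active and the sham sessions (Interventions).

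**The concern.** Receiving a first session happens after randomisation. Once membership of the primary set depends on it, the two groups compared are no longer exactly the groups that were randomised. The usual defence of such a set is that starting treatment cannot depend on the arm. That defence is complete when everyone concerned is blinded until the first dose. Here the person giving the first session knows the allocation, so the defence is good but not complete.

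Three features make this worth a comment:

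- **No check is planned.** On any ordinary definition a per-protocol set also excludes patients who had no session. The worst-case analysis is for categorical outcomes only, so it does not reach BAI or VAS.
- **Observed data would be discarded.** A non-starter who attends the week 4 and week 16 assessments is still excluded.
- **The wording pulls two ways.** The definition says that adherence and dropout do not matter, yet a patient who drops out before session 1 is excluded for that reason.

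At stake is the between-arm comparability of both primary contrasts in a trial of 60 patients.

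**Working it through.** **Inputs.** 30 patients per arm (Sample size). The article gives no expected number of non-starters. Its 20% dropout allowance is not split into losses before and after the first session. So two quantities are assumed: k, the number of non-starters, all in one arm; and d, the difference in SD units between their outcomes and those of the other patients in that arm. The plan has no figure of its own on this point to reproduce.

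**Size of the shift.** Dropping k patients who differ by d from the rest moves that arm's mean by k × d / 30. The standard error of a difference in means with 30 per arm is √(2/30) = 0.258 SD. With no true difference between the arms as randomised, the two-sided type I error is P(Z > 1.96 − shift/SE) + P(Z < −1.96 − shift/SE).

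| k (one arm only) | d | Shift (SD) | Shift / SE | Type I error |
|---|---|---|---|---|
| 0 | any | 0 | 0 | 5.0% |
| 1 | 1 | 1/30 = 0.033 | 0.13 | 5.2% |
| 2 | 1 | 2/30 = 0.067 | 0.26 | 5.8% |
| 3 | 1 | 3/30 = 0.10 | 0.39 | 6.7% |

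An exact calculation with the noncentral t distribution, the reduced arm size and d measured from the full arm's mean (shift = k × d / (30 − k)) gives 5.2%, 5.8% and 7.0% for k = 1, 2 and 3 at d = 1. At d = 0.5 it gives 5.1%, 5.2% and 5.5%.

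**Would the planned imputation be enough?** Take k = 3 and d = 1, and let m be the mean of the 27 starters in the affected arm.

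- *No post-baseline data from non-starters, imputation under missing at random.* The imputed values average m, so the arm mean is (27m + 3m)/30 = m, the same as in the modified set.
- *All three non-starters observed.* The arm mean is (27m + 3(m − 1))/30 = m − 0.10, and the full 0.10 SD is recovered.

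For partial follow-up take k = 2, so 28 starters, with one of the two non-starters observed. The other is imputed around (28m + (m − 1))/29 = m − 0.034. The arm mean is then m − (1 + 0.034)/30 = m − 0.034, about half of the 0.067 SD.

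A simulation confirms this with baseline adjustment (30 per arm; baseline–outcome correlation 0.5 assumed; non-starters 1 SD lower for reasons that baseline does not explain). Contrasts are in SD:

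| k | True effect in starters | Modified set | All randomised, imputed | All randomised, observed |
|---|---|---|---|---|
| 2 | 0 | 0.000 | 0.000 | −0.067 |
| 3 | 0 | −0.002 | −0.002 | −0.103 |
| 3 | 0.8 | 0.800 | 0.801 | 0.701 |

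Imputation from baseline alone reproduces the modified-set answer. It neither removes the bias nor dilutes the effect.

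**The case against.** The strongest reply has four parts.

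1. **Operators are not said to control entry.** A reader might infer that unblinded acupuncturists decide who is analysed. The article does not support that. It requires only that a session was received, and it gives the acupuncturist no say in who starts. Patients are blinded, the sham device displays the same parameters as the active one, and treatment is free. Ordinary failure to attend should therefore not depend on the arm. This stands, and what remains is possible influence.
2. **The set is openly labelled as modified.** The phrase about adherence and dropout can be read as applying after the first session. This is a fair reading, so the phrase needs clarifying and is not in itself a serious error.
3. **Summarising baseline for all randomised patients is good reporting.** This also stands. The difference between the two sets only shows that the plan keeps non-starters in the baseline table and in no efficacy analysis.
4. **The risk is small.** Even a type I error of 5.8% needs two non-starters in one arm, none in the other, each 1 SD different. This stands too.

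None of this explains why observed outcomes should be discarded, or supplies an analysis that would reveal a differential loss. Whether the set agrees with the reporting guideline cited for it needs an outside source and is not judged here.

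**Conclusion.** The point holds in a limited form. The primary set is conditioned on a post-randomisation event that people who know the allocation could in principle influence, and no planned efficacy analysis would detect a resulting imbalance. The shift is 0.07 to 0.10 SD, with a type I error of about 5.8% to 6.7% (up to 7.0% by the exact calculation), if 2 or 3 of 30 patients are lost from one arm only and each differs by 1 SD. Both values are assumptions. With 0 or 1 non-starter the effect is negligible, and with similar losses in both arms the shifts would largely cancel.

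Two stronger conclusions do not follow. The documents do not show that selection by operators will occur. Nor would it be enough to rename the set and impute from baseline, because under missing at random that returns the modified-set result. The change is worth making because it costs little, not because the present plan is likely to mislead.

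**What to change.** In Statistical methods:

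- Define the primary set as all randomised participants, analysed in the arm to which they were assigned.
- Seek and use the already scheduled week 4 and week 16 BAI and VAS from patients who never start.
- Use the planned multiple imputation only for values still missing. Add a sensitivity analysis that does not assume non-starters respond like treated patients in their arm, for example reference-based or delta-adjusted imputation.
- Keep the one-session set as a sensitivity analysis.
- Report the number of non-starters by arm, with reasons.
- Reword the phrase about adherence and dropout so that it does not describe a set that excludes non-starters.

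**Cost.** A few sentences of text, some effort to obtain scores from the few non-starters, and a little more analysis. No extra patients or scheduled visits are needed. Where non-starters' outcomes are observed, the estimated effect may be slightly smaller.

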**Figure 1 F1:**
[figure not shown]
Study design. EA, Electroacupuncture. Rescue medication will be allowed throughout the trial (baseline, treatment phase, follow-up phase), with a maximum daily dosage of 600 mg. The timing and dosage of all rescue medications will be recorded.

**Table 1 T1:** Schedule of enrolment, treatments, and assessments.

Study period	Screening	Baseline	Treatment period	Follow-up period
		Week−2-0	Week 4	Week 16
Eligibility screening	^ ***** ^			
Demographic data	^ ***** ^			
Case data	^ ***** ^			
History of TN	^ ***** ^			
History of treatment	^ ***** ^			
Inclusion criteria	^ ***** ^			
Exclusion criteria	^ ***** ^			
Informed consent	^ ***** ^			
Treatment condition			^ ***** ^	
Outcome assessment				
(1) BAI		^ ***** ^	^ ***** ^	^ ***** ^
(2) VAS		^ ***** ^	^ ***** ^	^ ***** ^
(3) BPI-facial		^ ***** ^	^ ***** ^	^ ***** ^
Safety assessment			^ ***** ^	^ ***** ^
Recurrence				^ ***** ^

^*^Required; BAI, Beck Anxiety Inventory; VAS, Visual Analog Scale; BPI-Facial, Brief Pain Inventory-Facial Scale.

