### Rescue medications

During all three phases of this study, including the 2-week baseline period, 4-week treatment period, and 12-week follow-up period, participants will not receive any treatment other than rescue medication. However, rescue medication will be allowed according to the Declaration of Helsinki for patients experiencing intractable pain. Participants will be allowed to take 200 mg of CBZ after meals, with a maximum dose of 600 mg per day in this study. Rescue medication was administered if the VAS score was ≥5 and persisted for more than 2 h. For each administration, the time and dose were recorded in detail. These recording procedures were predefined.

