### Outcome assessment

#### Primary outcomes

This study adopted dual primary endpoints: changes in BAI score and VAS score from baseline to week 4 post-treatment and week 16 follow-up phase, to fully assess the proposed “dual regulatory effect” of EA in TN patients with anxiety.

The BAI is a widely used anxiety scale for psychological assessment of patients and self-assessment in the general population. It was created by the team of American scholar Aaron T. Beck in 1988, with a total of 21 self-report questions (34). Notably, the scale is primarily designed to measure the degree of anxiety and to evaluate the therapeutic effects of anxiety treatment. The BAI adopted the 4-point Likert scale, ranging from 0 to 3 points for each question, based on the following criteria: ‘0′ means not at all; ‘1′ means mildly, with little annoyance; ‘2′ means moderately, feeling uncomfortable but tolerable; ‘3′ means severely, unbearable. The total score is the sum of all questions, ranging from 0 to 63 points, with a higher total score indicating a greater degree of anxiety. Generally, a participant with a total score between 0 to 7 points is considered to have basically no anxiety symptoms, while 8 to 15 points means mild anxiety, 16 to 25 points is moderate anxiety, and above 26 by severe anxiety.

Pain intensity will be evaluated using a 10-cm VAS anchored by ‘0′ (no pain) on the left and ‘10′ (worst pain imaginable) on the right. Participants will be asked to mark the point on the line that best represents their current pain intensity. The distance in centimeters from the ‘0′ end to the mark will be measured and recorded as the pain score. The *International Association for the Study of Pain (IASP)* recommends using the VAS score to assess pain intensity in patients with neuropathic pain, and to validate pain intensity relief with a particular therapy in a clinical trial (Grade A) (35).

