EA enhances pain relief and diminishes anxiety scores among patients with TN (4, 46). The mechanism may be related to the following reasons: (1) Through the modulation of opioid peptides, 5-hydroxytryptamine, norepinephrine, glutamate receptors and their transporters, cytokines, and signaling molecules, EA collectively inhibits nociception and emotional responses (47). Among them, opioid peptides play a central role in EA-induced suppression of various types of pain (48–50). (2) The anterior cingulate cortex (ACC) occupies a pivotal position in the interaction between pain and anxiety (51). Evidence shows that EA alleviated pain-related anxiety by inhibiting the PKCzeta/protein kinase Mzeta-GluR1 pathway in the ACC and increasing the n-methyl-d-aspartate receptor pathway in the prefrontal cortex, hippocampus and hypothalamus (52, 53). Further, pain-induced anxiety-like behaviors could also be reduced by EA treatment by activating the rostral ACC-thalamus circuit, suppressing the dopamine D2 receptor pathway in basolateral amygdala (54). (3) The hippocampus is really important for controlling pain and mood (55). Injury and inflammation, for example, can cause changes to the structure and function of hippocampal synapses by activating pain circuits for a prolonged, which can then lead to anxiety-like behaviors (56, 57). Liu et al. showed that EA can encourage the repair and remodeling of hippocampus neurons by increasing the level of factors related to hippocampus' nucleus, balancing iron metabolism and decreasing lipid peroxidation (58). Furthermore, EA reversed synaptic damage by restoring dendritic density and morphology in the hippocampus, producing analgesic and anxiolytic effects (59). In summary, EA achieves simultaneous improvement of pain relief and emotional disorders by acting synergistically on the peripheral, central and limbic systems at multiple targets, particularly by modulating key neuralcircuits.

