The EA intervention in this protocol is based on our group's prior clinical studies of EA for TN (4, 33). These studies have demonstrated that EA is superior to CBZ in reducing pain intensity, enhancing facial motor function, and improving quality of life in patients with TN. The protocol also complies with the Evidence-Based Clinical Practice Guidelines for Acupuncture: TN (T/CAAM 018-2015) (60). Local acupoint stimulation acts directly on the trigeminal nerve pathway. It produces analgesia through C-fiber convergence in the nucleus of the solitary tract, stimulates the nerve trunk to promote endorphin release, and improves microcirculation (61, 62). Additionally, EA can modulate synaptic plasticity in the hippocampal CA1 region, thereby alleviating orofacial pain and anxiety (59). The use of alternating 2 Hz and 100 Hz stimulation stimulates the release of multiple opioid peptides, including enkephalins, β-endorphin, and dynorphin, thereby enhancing the analgesic effect (63).

A rescue dose of CBZ up to 600 mg/day was permitted for breakthrough pain management to prevent treatment discontinuation. While EFNS guidelines recommend a therapeutic range from 200 to 1,200 mg/day (64–66), doses exceeding 600 mg/day increase AEs, including drowsiness, dizziness, and postural instability, etc. A study of 354 patients with TN reported a 43.6% AEs incidence at 600–800 mg/day (67), consistent with previous safety reports(64). Therefore, clear criteria was established in this trial for rescue medication administration, and all medication use was documented in detail. Rescue medication doses will be included as covariates in the analysis to control for potential confounding.

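### The primary analysis adjusts for rescue carbamazepine taken after randomisation, which treatment is expected to change, so it does not estimate the effect of assignment to electroacupuncture

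*Protocol article*

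**What the plan says.** The Statistical methods section of the protocol article states that "rescue medication (CBZ) use will be included as a time-varying covariate in primary analyses (e.g., mixed-effects models or ANCOVA" and gives the purpose as "to control for its impact on BAI scores". It adds that "sensitivity analyses will stratify participants by rescue medication status (CBZ users vs. non-users) to evaluate whether treatment effects persist independently of CBZ exposure". The Discussion repeats the adjustment, this time by dose: "Rescue medication doses will be included as covariates in the analysis to control for potential confounding".

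The Rescue medications section sets the trigger: "Rescue medication was administered if the VAS score was ≥5 and persisted for more than 2 h". The caption of Figure 1 says "Rescue medication will be allowed throughout the trial (baseline, treatment phase, follow-up phase", so most of the period in which rescue can be taken lies after randomisation. The dual primary endpoints are "changes in BAI score and VAS score from baseline to week 4 post-treatment and week 16 follow-up phase". The Discussion states the expected action of the treatment: "EA enhances pain relief and diminishes anxiety scores among patients with TN".

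The article names no primary analysis without the CBZ covariate and states no estimand that would call for it.

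**The concern.** Randomisation already removes confounding between arm and outcome at baseline. A variable measured later cannot confound assignment, but it can be changed by it. Here the trigger for rescue is the pain scale that also serves as a co-primary endpoint, and EA is expected to lower pain. If EA works, fewer EA patients should reach the trigger and take CBZ.

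Holding CBZ use fixed does two things. It removes the part of the EA effect that shows up as less pain and hence less rescue. It also compares unlike patients: an EA patient who still needs rescue is likely to be a more severe case than a sham patient who needs it. The user/non-user analysis does the same by splitting, because each stratum is selected after randomisation. It cannot show an effect that is independent of CBZ, so it is no check on the primary model.

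At stake is whether the trial's main estimate answers its question, the effect of EA against sham on anxiety and pain.

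**Working it through.** **Step 1. The text, side by side.** A time-varying covariate takes in CBZ use after randomisation, not only use in the 2-week baseline phase. The words introduced by *e.g.* leave the model open, not the covariate. The trigger is VAS at or above 5 for more than 2 hours, and change in VAS is co-primary. The Discussion expects EA to reduce pain. Together these put later CBZ use downstream of treatment. That EA changes rescue use is an inference from the trigger and the expected pain relief; the article does not say it outright.

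**Step 2. Size.** The article gives no rescue rate, no CBZ effect on either scale and no expected EA effect on VAS or BAI, so there is no planned figure to reproduce. The size was explored by simulation, and every input in this step is an assumption:
- Latent severity U has SD 1.5. Baseline VAS is about 6.5 + U, limited to 4–10.
- On-treatment pain before rescue: L = 5.5 + 0.7U + noise (SD 1.5) − a for EA, where a is the EA effect on pain.
- Rescue R = 1 if L + noise (SD 0.7) ≥ 5.
- VAS = L − c·R + noise (SD 0.8), where c is the CBZ effect in cm.
- BAI = 0.5 × baseline BAI + 10 + 2(VAS − 5) − d for EA + noise (SD 4), where d is a direct EA effect on BAI.
- Analysis: ANCOVA of change on arm and baseline score, without and then with R, on 300,000 patients per arm. R is a single yes/no indicator at one visit, simpler than a time-varying covariate.

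Share lost = 1 − (estimate with R ÷ estimate without R). With d = 0:

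| a (cm) | Rescue, sham / EA | c (cm) | VAS without → with R | Lost | BAI without → with R | Lost |
|---|---|---|---|---|---|---|
| 1 | 60% / 40% | 0 | −1.00 → −0.52 | 48% | −2.01 → −0.93 | 54% |
| 1 | 60% / 40% | 1 | −0.80 → −0.52 | 35% | −1.62 → −0.95 | 41% |
| 1 | 60% / 40% | 2 | −0.60 → −0.52 | 13% | −1.19 → −0.92 | 23% |
| 2 | 60% / 22% | 0 | −1.99 → −1.07 | 46% | −3.98 → −1.89 | 53% |
| 2 | 60% / 22% | 1 | −1.61 → −1.08 | 33% | −3.24 → −1.91 | 41% |
| 2 | 60% / 22% | 2 | −1.24 → −1.08 | 13% | −2.50 → −1.93 | 23% |

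With a direct effect on BAI added (d = 1 with a = 1, d = 2 with a = 2), the BAI loss was 12% to 36%: for example, −2.19 → −1.92 gives 1 − 1.92/2.19 = 12%, and −2.99 → −1.91 gives 1 − 1.91/2.99 = 36%.

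**Step 3. Does adjustment recover the effect had nobody taken rescue?** In the table's scenarios that effect is −1 or −2 cm on VAS and −2 or −4 points on BAI. The adjusted values, about −0.5 or −1.1 cm and −0.9 or −1.9 points, miss it as well.

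**Step 4. Strata.** With a = 2, c = 1, d = 0, the BAI effect was −1.67 in users and −2.05 in non-users, against −3.24 overall. Both are shrunken, with the sign unchanged.

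**Step 5. Power at 30 per arm (3,000 trials, c = 1, d = 0).** With a = 1, VAS fell from 50% to 27% and BAI from 20% to 10%. With a = 2, VAS fell from 98% to 71% and BAI from 65% to 27%.

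**Step 6. No effect on pain.** With a = 0 and d = 0, rescue is 60% in both arms, both models give zero and rejection stays near 5%.

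**Step 7. Other assumptions.** Two further runs with different coefficients, with baseline BAI and pain in the model, lost 2–52% of the BAI effect in one, and 42–51% (BAI) and 23–36% (VAS) in the other.

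**The case against.** The strongest defence is that CBZ may itself act on BAI, so unequal use would blur what EA does, and the authors want that removed. The worry is fair, but a covariate does not meet it. No effect-without-rescue estimand is stated, and in Step 3 the adjusted estimate did not recover one.

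A second objection concerns scope. The stated purpose names BAI only. The plural in *primary analyses*, with two co-primary endpoints, suggests that VAS is included, but this is a reading and not a certainty. The trigger is also not the endpoint: it needs pain that persists for over 2 hours, whereas the endpoint is current pain at a visit. They are related, not identical. This qualifies the VAS part and leaves the BAI part intact.

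Third, the split by users and non-users is labelled a sensitivity analysis and does not decide the trial. That stands, and relabelling it as descriptive would be enough.

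Fourth, a reader might infer that the adjustment wipes out nearly all the benefit, reverses its sign among CBZ users, or makes a false claim of efficacy likely. The documents do not support this. They give no rates from which any size follows. Near-total loss appears when baseline scores are left out of the model, but the endpoints are changes from baseline and the models named would normally carry them. With baseline scores included, the strata kept the right sign. In the case where EA lowers pain but leaves BAI unchanged, rejection was 5–8% and the excess went against EA. That case also sits awkwardly with the article's premise that pain and anxiety move together.

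**Conclusion.** The point holds. As written, the primary model conditions on a consequence of treatment, and the sensitivity analysis meant to support it does the same. The BAI estimate would not be the effect of assignment to EA, and the VAS estimate would not be either if the adjustment extends to it.

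The size cannot be computed from the documents. Under the assumptions shown it runs from none, when EA changes neither pain nor rescue use, to about half of the effect. In those scenarios the bias is towards no effect, so the main risk is lost power and a missed benefit. Other causal structures could change the direction. Severe bias is therefore a possibility under assumptions, not a demonstrated figure. The error itself does not depend on the simulated sizes and should be corrected before the analysis.

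**What to change.** - Make the primary comparison by randomised group regardless of rescue use, with baseline-only covariates: the baseline score and, if wanted, rescue use in the 2-week baseline phase before randomisation. Remove CBZ use after randomisation from the primary model, and remove the confounding rationale from the Discussion.
- Report CBZ use by arm as a secondary outcome: any use, and cumulative dose to week 4 and week 16. Time and dose of each administration are already recorded.
- Label the user/non-user results as descriptive only, or replace them with a sensitivity analysis over all patients in the modified ITT population. If an effect without rescue is of interest, define it as a supplementary estimand with a method suited to it.

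The cost is wording in the protocol and analysis plan; no new data are needed and no rule on giving rescue changes. The downside is that the primary estimate then includes any effect of unequal CBZ use between arms, which the comparison of CBZ use makes visible.

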### Sample size

Sample size estimation was performed by the “*Powerandsamplesize.com*” online website (31). This study is the first to explore the therapeutic effect of EA for TN with anxiety. Based on our pilot data with emotion scores between groups [EA group: 3.9 (1.2); control group: 1.2 (0.8)] by using an independent two-sample *t-*test design, a minimum of 25 participants per group will be required (two-sided α = 0.05, power = 0.8). To account for a 20% dropout rate, the final sample size will be set to 30 per group (total *N* = 60). This ensures adequate power even with potential attrition.

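### Two analysis rules for the continuous outcomes cannot both be followed for BAI and VAS change, and no single primary model is named

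*Protocol article*

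**What the plan says.** The Primary outcomes section defines two primary endpoints, change from baseline in BAI and in VAS, each at week 4 and week 16.

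The Statistical methods section then gives two rules that reach these endpoints.

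- **First paragraph.** It states that "rescue medication (CBZ) use will be included as a time-varying covariate in primary analyses (e.g., mixed-effects models or ANCOVA"), and gives control of the effect on BAI as the reason. The models are examples, not a choice. The Discussion repeats that rescue doses will be covariates. The same paragraph plans multiple imputation for missing continuous outcomes.
- **Second paragraph.** "For measurement data, normality is first assessed". Normal data go to t-tests, paired t-tests, "analysis of variance, or analysis of covariance, while non-normally distributed data will be analyzed using" rank-sum tests, with Mann-Whitney and Wilcoxon signed-rank as the examples. Nothing takes BAI or VAS change out of this rule.

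The Sample size section sizes the trial "by using an independent two-sample" t-test, which has no covariate. The baseline score is not named as a covariate in any of these places.

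**The concern.** BAI and VAS change are measurement data, so both paragraphs apply to them. An analyst who follows the second paragraph can arrive at a test that cannot honour the first. The listed tests also answer different questions: some adjust for baseline and some do not, some yield a mean difference and some do not, and two compare within an arm instead of between arms.

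Two things are at stake. An unadjusted test would leave unused the baseline scores that a 60-patient trial already collects. And where the text permits several tests for one endpoint, a reader of the results cannot tell whether the reported test was fixed in advance.

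**Working it through.** **1. The two rules side by side**

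| Listed method | Carries a CBZ covariate? | Adjusts for baseline score? | Compares EA with sham? |
|---|---|---|---|
| Mixed model (first paragraph only) | yes, time-varying | if specified | yes |
| ANCOVA (both paragraphs) | yes; at one visit only as one value per patient | if specified | yes |
| ANOVA | no | no | yes |
| Two-sample t-test on change | no | no, only subtracts it | yes |
| Mann-Whitney on change | no | no, only subtracts it | yes |
| Paired t-test, Wilcoxon signed-rank | no | no | no, within arm |

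On the normal branch the rules can be reconciled by choosing ANCOVA. On the non-normal branch only rank tests are offered, and none carries the covariate that the first paragraph requires. That is the direct conflict.

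Two further mismatches follow. Standard pooling after multiple imputation combines an estimate with its standard error, and a plain rank test reports neither, so it fits poorly with the imputation plan. And because patients enter on VAS of at least 4 and BAI of at least 16, regression to the mean favours improvement in both arms, so paired tests are likely to look favourable in each arm whatever EA does relative to sham.

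**2. The plan's own sample-size figure**

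Inputs (Sample size section): "EA group: 3.9 (1.2); control group: 1.2 (0.8"), "two-sided α = 0.05, power = 0.8", and "a minimum of 25 participants per group will be required".

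- Difference: 3.9 − 1.2 = 2.7. Pooled SD: √[(1.2² + 0.8²)/2] = √1.04 = 1.02. Standardised effect: 2.7/1.02 ≈ 2.65.
- n per group = 2(1.96 + 0.84)² × 1.04/2.7² ≈ 2.24, rounded up to 3 (normal approximation; 4 to 5 by the exact t-test with SD 1.02 or 1.2).

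The stated 25 is not reproduced. That is a separate defect. It matters here because power at 25 per group exceeds 0.999 at the pilot effect for the unadjusted t-test already, so no loss can be shown there. The standardised effect at which 25 per group gives 80% power is √[2(1.96 + 0.84)²/25] ≈ 0.79.

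**3. Cost of an unadjusted change-score t-test**

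Let r be the baseline-outcome correlation, with equal baseline and outcome variance σ². The article gives no r, so the values below are assumptions.

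- Variance of the change score: 2(1 − r)σ².
- Residual variance after baseline adjustment: (1 − r²)σ².
- Ratio: (1 − r²)/[2(1 − r)] = (1 + r)/2.

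If the change-score t-test has 80% power, the adjusted analysis has power Φ[(1.96 + 0.84)/√((1 + r)/2) − 1.96].

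| r | Variance ratio | Power of adjusted analysis |
|---|---|---|
| 0.3 | 0.65 | 94% |
| 0.5 | 0.75 | 90% |
| 0.7 | 0.85 | 86% |

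**4. Type I error**

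Null trials were simulated at 25 per group.

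- *Check followed mechanically* (Shapiro-Wilk at 5% in each arm, then a change-score t-test or Mann-Whitney; normal and skewed errors; r = 0.3, 0.5, 0.7; 6,000 trials per setting): 4.8% to 5.4%.
- *Smallest p-value of change-score t-test, ANCOVA and Mann-Whitney* (normal errors, r = 0.5, 10,000 trials): 5.0%, 5.0% and 4.8% singly, 8.0% for the best of the three. Repeating this at r = 0.3 and 0.7 also gave about 8%.
- *Adding a final-score t-test to the choice:* 10% to 12% per endpoint and visit.

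**The case against.** Only the first paragraph uses the term primary analyses. The second reads as a general list by data type that must also serve baseline tables and BPI-Facial, and ANCOVA stands in both. On that view there is one primary approach, loosely worded, followed by generic text. This stands in part: a reader might infer two rival primary analyses, and the article does not go that far. What remains is that the second paragraph does not exempt the primary endpoints, and its non-normal branch offers no method that meets the first.

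Model terms, including baseline covariates, are commonly left to an analysis plan that is not shown. That is fair. Silence on baseline adjustment would be no finding by itself; it is relevant here because the stated options differ on exactly that point.

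A reader might also infer that the trial loses power. The article does not commit to the change-score t-test, so the loss is conditional on that choice and on r.

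A reader might finally infer that the normality check inflates type I error. It does not when followed as written, because it selects on distributional shape and not on the p-value. Taking the smallest p-value is not planned, and the statistician is to be blinded, which limits selection by result.

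Two technical limits also stand. A single-visit ANCOVA could carry CBZ use summed to that visit, though not as a time-varying term. Rank-based effect estimates with standard errors can be pooled after imputation, so that mismatch is practical and not absolute.

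**Conclusion.** The point holds as a conflict between stated rules, not merely as missing detail. For BAI and VAS change the two paragraphs cannot both be followed whenever a t-test, ANOVA or rank test is used, and on the non-normal branch a rank test is what the text requires. No single primary model is fixed.

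The sizes are conditional. Baseline adjustment would raise power from 80% to about 86% to 94% for r from 0.7 down to 0.3, assuming equal variances and an unadjusted change-score t-test as the alternative. At the article's own pilot effect the gain vanishes, although that effect does not lead to the stated 25 per group and so is weak reassurance. Type I error is near 5% under mechanical use and about 8% under free choice among three tests.

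This should be corrected. It does not invalidate the design.

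**What to change.** Before unblinding, name one primary model for each of BAI and VAS. A suitable one is a mixed model of the week 4 and week 16 scores with arm, visit, arm-by-visit and that endpoint's baseline score, reporting the between-arm difference with a 95% confidence interval at both visits that the Primary outcomes section names.

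- Exempt the primary endpoints from the normality check. Inspect residuals, and keep rank-based methods as sensitivity analyses.
- Do not base efficacy conclusions on paired within-arm tests.
- State explicitly how the CBZ covariate promised in Statistical methods and the Discussion is handled. Whether to adjust for use after randomisation is a separate question that this point does not settle.

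The cost is wording in the protocol or analysis plan. The scores are already collected at baseline, week 4 and week 16, and the model can be fitted in the planned SPSS 25.
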